#### Data analysis

The statistical analysis will be carried out by the main researcher and will be performed using SPSS version 23.0 and Excel version 18.11 software. We will employ standard descriptive statistics for the basic characteristics of the population and the distributions of the scores of the tests (means, standard deviations, etc.). We will use *t* tests to explore the equality of means for total scores of POS and CANHELP Lite between different pairs (e.g., COPD patients vs COPD caregivers). To compare continuous variables between the different study groups, we will use Fisher’s exact tests and Mann-Whitney *U* test. Finally, we will use Mann-Whitney *U* tests and Wilcoxon signed-rank tests in order to analyze individual questions that will be treated as ordinal variables, while 95% confidence intervals will also be presented. Missing data will be included in the analysis, and their implications will be clarified.

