## Aim

The aim of this study is twofold: (1) to assess the feasibility of administering an early PC intervention in cardiology and pulmonology wards and (2) to measure the potential benefits of an early PC intervention in CHF/COPD patients in their QoL and satisfaction of care. Additionally, the objectives of this study are as follows:i)To identify barriers in administering an early integrated PC intervention in an acute settingii)To examine the appropriateness of the eligibility (referral) criteriaiii)To measure whether and to what extent patients and their informal caregivers share common beliefs on QoL and quality of careiv)To test the hypothesis that early integration of PC in CHF/COPD can improve QoL and quality of carev)To identify the PC needs of the targeted population

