**Fig. 1 Fig1:**
[figure not shown]
Sequence of the feasibility before-after intervention study

In both groups (control and intervention), patients and their most important informal caregiver will be asked to complete the Canadian Health Care Evaluation Project (CANHELP Lite) Questionnaire [28], the Palliative Outcome Scale (POS) Questionnaire [29], and the Advance Care Planning Questionnaire developed by the Palliative Support Team (at the University Hospital Leuven) to measure the current level of integrated PC in the following two timings: (i) inclusion moment after signing the informed consent and (ii) 3 months after inclusion (for both baseline and intervention groups). The methodology of this study was developed based on the SPIRIT guidelines.

We decided to jointly study CHF and COPD due to the fact that these two chronic, high prevalence, and non-malignant diseases share heavy physical and psychosocial symptom burden and similarly complicated disease trajectories, and currently, they are not curable [30, 31]. Moreover, there is also empirical evidence that CHF/COPD specialists share similar views on the role of integrated PC for these two diseases [32].

Currently in our hospital, the acute wards outside oncology have access to the Palliative Support Team, but they typically call for it only in the last hours (in the best case, in the last 2–3 days) of a patient’s life. The personnel of the cardiology and pulmonology wards have no training on the provision of PC.

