### Sample size

A convenience sample of 50 patients and 50 informal caregivers per phase (25 CHF and 25 COPD patients and their informal caregivers for the baseline phase and 25 CHF and 25 COPD patients and their informal caregivers for the intervention phase) has been set as a target based on the following rationale. We use as a reference a two-sample *t* test on the total POS scores, assuming a minimally relevant difference of 4, i.e., 10% of the best score 40, and a common standard deviation of 6, which constitutes the worst case based on previous studies [33, 34]. In order to obtain 80% power at a significance level of 5%, a total of 37 patients per group will be required. To this number, we will add a 30% attrition rate which results in 50 patients and caregivers per group. We will retrospectively compute our standard deviation with an interim analysis once three fourths of the originally planned sample size has been collected to examine whether upward revisions are required.

It is important to note that due to the shortage of studies similar to ours, attrition rates for the population of interest are not well understood. As a starting point, we have used attrition rates from integrated palliative care cancer studies and we aim to retrospectively evaluate the suitability of these rates.

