### Informed consent

The main researcher will explain the study protocol to both the patient who meets the inclusion criteria and his/her most important informal caregiver. The patient and the informal caregiver will receive the informed consent and a letter with the description of the study. After 1 or 2 days of reflection time, the researcher (NS) will contact them again personally to ask if they like to join the study, which means that (a) they will have the patient’s electronic records searched and (b) both patients and informal caregivers will be asked to fill in two questionnaires at inclusion and 3 months after inclusion. If the patient and informal caregiver decide to participate in the study, they will provide a signed consent. If there is no informal caregiver or the informal caregiver does not want to participate, then we will still include the patient in the study.

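### Objective iii asks how far patients and their own caregivers agree, but the t tests of equal means named for their total scores cannot measure agreement

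*Protocol article*

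**What the plan says.** The Aim section lists five additional objectives. The third is to measure "whether and to what extent patients and their informal caregivers share common beliefs on QoL" and on quality of care. The data are linked by design: under Methodology and study design, "patients and their most important informal caregiver will be asked to complete" the three questionnaires, at inclusion and at 3 months.

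The Data analysis section plans t tests to "explore the equality of means for total scores of POS and CANHELP Lite between different pairs (e.g., COPD patients vs COPD caregivers"). It does not say whether these tests are paired or two-sample. At item level, "we will use Mann-Whitney *U* tests and Wilcoxon signed-rank tests in order to analyze individual questions that will be treated as ordinal variables", without saying which contrast each test serves. No measure of agreement is named.

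Three other places bear on the point:

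- Sample size is based on a two-sample t test on total POS.
- Informed consent states: "If there is no informal caregiver or the informal caregiver does not want to participate, then we will still include the patient in the study".
- Questionnaires says that POS has the same 12 questions for patients and caregivers, while CANHELP Lite has 21 questions for patients and 23 for caregivers.

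**The concern.** Whether, and how far, a patient and his or her own caregiver hold the same view is a question about agreement within each dyad. A comparison of means asks something else: whether caregivers as a body score higher or lower than patients as a body. Two sets of scores can have the same mean while individual dyads disagree widely, because overestimates in some dyads offset underestimates in others.

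At stake is the reading of the result. A non-significant t test could be reported as patients and caregivers sharing common beliefs when it carries no such information. A significant test would show a shift in level but not how closely dyads track each other.

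A lesser matter is precision. If a two-sample test were applied to linked scores, it would use the wrong variance for the difference.

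**Working it through.** **Inputs from the protocol (Sample size).** SD of total POS 6; relevant difference 4; 25 patients with caregivers per disease per phase; 5% significance (two-sided assumed); 80% power.

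**Assumed.** The within-dyad correlation ρ is not in the document, so a range is shown. Caregiver scores are given the same SD of 6, and differences are treated as normal. The 4 points are the protocol's relevant difference between groups. They serve here only as a yardstick for closeness within a dyad.

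**Step 1: the protocol's own figure.** The normal approximation is 2(1.960 + 0.842)² × 6²/4² = 35.3, rounded up to 36. The exact two-sample t test gives 36.3, rounded up to 37. The stated 37 per group reproduces.

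**Step 2: what a mean test can see.** For a dyad difference d with mean zero, SD_d = 6√(2(1 − ρ)). The 95% limits of agreement are ±1.96 × SD_d, and the share of dyads within 4 points is 2Φ(4/SD_d) − 1.

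| ρ (assumed) | SD_d | Limits of agreement | Dyads within 4 points | Paired t test rejects |
|---|---|---|---|---|
| 0 | 8.49 | ±16.6 | 36% | 5% |
| 0.3 | 7.10 | ±13.9 | 43% | 5% |
| 0.5 | 6.00 | ±11.8 | 50% | 5% |
| 0.7 | 4.65 | ±9.1 | 61% | 5% |
| 0.9 | 2.68 | ±5.3 | 86% | 5% |

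The last column is 5% by construction, because the means are equal. The test responds to a shift in means and to nothing else, so it cannot separate the first row from the last. With equal means and equal SDs the intraclass correlation equals ρ, so an agreement measure does separate them.

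**Step 3: if the t tests are two-sample.** The real type I error of a two-sample test on paired scores is about 2(1 − Φ(1.96/√(1 − ρ))), which gives 1.9% at ρ = 0.3 and 0.6% at ρ = 0.5. Simulation with 25 dyads (20,000 runs) gave 2.0% and 0.8%.

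Power for a 4-point difference, with the paired test from the noncentral t (noncentrality 4√n/SD_d) and the two-sample test by simulation on the paired data:

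| Dyads | ρ (assumed) | Two-sample | Paired |
|---|---|---|---|
| 25 (one disease, one phase) | 0.3 | 66% | 77% |
| 25 | 0.5 | 69% | 89% |
| 50 | 0.3 | 94% | 97% |
| 50 | 0.5 | 97% | 99.6% |

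The loss is material for a single disease in a single phase and small with 50 dyads. These are full-enrolment numbers, before attrition or missing caregivers.

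**The case against.** The strongest reply has three parts.

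- **The t tests are not expressly tied to objective iii.** They are offered as exploratory, and an agreement analysis could sit in a fuller document that is not shown. This carries some weight. Even so, the article does name a method for patient-caregiver total scores, its own example is exactly that contrast, and the method does not measure what the objective asks.
- **The plan may well respect the dyad.** A reader might infer that it treats patients and caregivers as independent and so produces wrong standard errors. The text does not establish this. Both variants are t tests, the section does not say which is meant, and signed-rank tests, a paired method, are listed for individual questions. The two-sample test under Sample size is a reference for sizing groups of patients and does not settle this contrast. This part of the objection stands: the text is ambiguous and is not a stated error. Nor would a two-sample test raise the false-positive rate under positive correlation. It would be conservative, with intervals that are too wide. Only negative correlation would reverse that (about 8.6% type I error at ρ = −0.3).
- **Patients without a caregiver may not enter the contrast.** A reader might infer that all patients will be compared with the caregivers of only some of them. The Informed consent section says only that such patients are still enrolled, not that they are used in this comparison. This also stands.

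**Conclusion.** The point holds in a limited form. Objective iii has no matching named analysis: t tests of equal means, paired or not, can show a systematic shift between patients and caregivers but not the extent to which they agree. This conclusion does not depend on how the t test is read or on any assumed correlation. The range from 36% to 86% of dyads within 4 POS points illustrates its size and rests on SD 6 for both parties, normal differences and assumed correlations from 0 to 0.9.

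The missing statement on pairing is secondary. It costs power only if a two-sample test is meant and the correlation is positive: about 11 percentage points (77% − 66%) to 20 points (89% − 69%) with 25 dyads.

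This should be fixed, but it is not critical. It concerns one of five additional objectives in a feasibility study and leaves the sample size, the control-intervention comparison and the feasibility assessment untouched.

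**What to change.** For objective iii, the Data analysis section should state that:

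- the analysis uses linked patient-caregiver dyads in which both responded, and the number of dyads is reported;
- agreement is reported with a 95% CI, as an intraclass correlation or limits of agreement for total POS and as weighted kappa for items that both versions share;
- the paired mean difference with its 95% CI is kept as a measure of systematic bias only, and a non-significant result is not read as agreement;
- CANHELP Lite is compared on per-item mean scores or matched items, because raw totals from 21 and 23 questions are not on a common scale;
- each signed-rank and Mann-Whitney test is assigned to its contrast (patient versus caregiver, inclusion versus 3 months, control versus intervention).

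The cost is a few sentences and slightly more analysis of data already being collected. Patients without a participating caregiver will not contribute to this objective, though they remain in all others that do not need a caregiver.

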## Methodology and study design

We propose to conduct a before-after intervention study consisting of three sequential phases: baseline phase, training phase, and intervention phase. During the baseline phase, the control group will receive standard care. During the training period, the personnel will be trained on how to use and apply the “early palliative care integration” intervention. Finally, during the intervention phase, the intervention group will receive the updated care (Fig. 1).

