### Data collection

The main researcher (NS) will explain the study protocol to both patient that meets the inclusion criteria and his/her most important informal caregiver. The patient will receive the informed consent document. After 1 or 2 days of reflection time, the main researcher will contact them again personally to ask if they like to join the study. If the patient and informal caregiver decide to participate in the study, they will provide their signed consent.

After the completion of the informed consent, the participants (patients and their informal caregiver) will be requested to fill in the three questionnaires in two timings: (1) at inclusion moment after signing the informed consent during the hospitalization of the patient and (2) at a follow-up of 3 months after inclusion (for both control and intervention groups). If a patient or an informal caregiver has difficulty understanding the questionnaires, the researcher in charge can provide additional information and help the participants fill in the questionnaires. When the eligible patients or their informal caregivers decline to participate, the researcher will ask for the reason and archive it. No special document will be provided to patients who will decline. Communication of the reason for not participating will be collected by the recruiter based on oral communication and without a predefined set of options in order to capture a broader spectrum of answers.

For the second measurement after 3 months, the same questionnaires will be sent by post to each patient and their caregiver and will be sent back to the researcher after they are completed. In some cases, the follow-up questionnaires will be administered to the patients when they visit the hospital for a checkup examination. When the follow-up questionnaires that have been posted are not returned back on time, the researchers will then contact the participants by telephone to remind them to complete and post the questionnaires back. The same process will be repeated for each patient and his/her caregiver for the intervention phase and after the implementation of the intervention. The study procedure for patients and their informal caregivers is described in Fig. 2.

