## Limitations

A limitation of this study is its design since we have decided against an RCT. We have extensively discussed the possibility for administering an RCT instead of a before-after study with all involved actors. However, the major obstacle for doing so was the fact that in both cardiology wards and pulmonology wards, there was a substantial overlapping of the intervention-involved personnel (psychologists, pastoral consultants). It was impossible to remove this bias given the organizational constraints of the wards, and for this reason, we decided that a before-after design would more controllable. The final report of our study will include recommendations for future RCT studies and guidelines on how to circumvent the emerging challenges.

Another limitation of this study is the use of the self-developed Advance Care Planning Questionnaire that has not yet been validated and published. This fact will be taken into consideration when performing the statistical analysis.

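### The only tests named are unadjusted, although the phases are non-randomised and inclusion POS, collected in both, could adjust the 3-month comparison

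*Protocol article*

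**What the plan says.** The Methodology and study design section sets out the sequence: "We propose to conduct a before-after intervention study consisting of three sequential phases: baseline phase, training phase, and intervention phase". The control group is recruited in the first phase and the intervention group in the last. The Limitations section acknowledges this: "A limitation of this study is its design since we have decided against an RCT".

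Under Data collection, patients and caregivers in both groups complete all three questionnaires, POS included, "at inclusion moment after signing the informed consent during the hospitalization of the patient", and again 3 months after inclusion. The Sample size section fixes the diagnostic mix of each phase, for example "25 CHF and 25 COPD patients and their informal caregivers for the intervention phase". It takes an unadjusted test as its basis: "We use as a reference a two-sample *t* test on the total POS scores".

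The Data analysis section lists t tests for POS and CANHELP Lite totals between different pairs (its example is COPD patients against COPD caregivers), Fisher's exact and Mann-Whitney tests between study groups, and Mann-Whitney and Wilcoxon signed-rank tests for individual questions. It names no regression, covariate or change-score comparison. On missing data it says: "Missing data will be included in the analysis, and their implications will be clarified".

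The Aim section includes a test of whether early palliative care improves quality of life and quality of care. The Expected results section speaks of quantifying the benefit.

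**The concern.** Without randomisation, nothing makes the two phases alike at inclusion. They are enrolled months apart, and the Recruitment section lets the team change the recruitment process if difficulties arise. If patients in one phase start with worse POS scores, an unadjusted comparison at 3 months counts part of that difference as an effect of the intervention, in whichever direction the imbalance runs.

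Inclusion POS is the obvious variable to adjust for: it is the same instrument, taken in the same patients, in both phases. Leaving it out of the between-phase comparison admits bias that could be avoided and gives up precision already paid for. The Post-feasibility study planning section makes a later randomised trial depend on encouraging outcomes, so the estimate has consequences.

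**Working it through.** **Inputs from the Sample size section.** Difference: "assuming a minimally relevant difference of 4, i.e., 10% of the best score 40". Spread: "a common standard deviation of 6, which constitutes the worst case based on previous studies". Power 80%, significance level 5%, 37 per group, 30% attrition, 50 per group.

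**Assumed inputs, not in the article.** Correlation r between inclusion and 3-month POS, 0.3 to 0.7. Equal SDs at the two times. A 2-point difference between phases in mean inclusion POS.

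**1. The plan's own figure.** The standardised difference is 4/6 = 0.667. A two-sided two-sample t test at 5% and 80% power needs 36.3, so 37 per group. This reproduces the stated number.

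**2. Power of the unadjusted test.** After 30% attrition, 50 × 0.70 = 35 per group remain. The noncentrality is 4/(6 × √(2/35)) = 2.79 on 68 degrees of freedom, which gives 78.5% power. At 37 per group it is 80.8%.

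**3. Bias from an imbalance at inclusion.** Under equal SDs, bias = r × (difference in mean inclusion POS). The false-positive rate is the two-sided rejection probability of the unadjusted t test at 35 per group when the true effect is zero, with noncentrality bias/(6 × √(2/35)).

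| r | Bias from a 2-point imbalance | Share of 4 points | False-positive rate |
|---|---|---|---|
| 0.3 | 0.6 | 15% | 7.0% |
| 0.5 | 1.0 | 25% | 10.6% |
| 0.7 | 1.4 | 35% | 16.1% |

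For scale, the standard error of the difference in mean inclusion POS with 50 per group is 6 × √(2/50) = 1.2. A gap of 2 points is 2/1.2 = 1.67 standard errors, which chance alone would produce or exceed in about 10% of studies, before any real change in case mix.

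**4. Power with adjustment.** Residual SD = 6 × √(1 − r²).

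| r | Residual SD | ANCOVA power, 35 per group | Completers per group for 80% |
|---|---|---|---|
| 0.3 | 5.72 | 82.2% | 34 |
| 0.5 | 5.20 | 88.8% | 28 |
| 0.7 | 4.28 | 97.1% | 20 |

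These figures take the phases as balanced at inclusion. A 2-point imbalance inflates the variance of the adjusted difference by 1 + (2² × 35/2)/(2 × 34 × 36) = 1.029, which costs about one percentage point of power or less.

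**5. Comparison of changes instead.** The SD of the change is 6 × √(2(1 − r)): 7.10, 6.00 and 4.65. Power at 35 per group is 64%, 78.5% and 94%. At r = 0.3 this is worse than the unadjusted test, so the form of adjustment matters.

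**The case against.** **The article may not commit to this comparison.** Its t tests are illustrated with patient-caregiver pairs, the two-sample t test is only a reference for the sample size, and covariates are often left to an analysis plan. This stands in part: the main between-phase test of POS total is not clearly fixed. But the article does list its methods, and every one that could compare phases is unadjusted.

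**Inclusion POS may not be wholly ignored.** The Wilcoxon signed-rank test is paired and may set inclusion against 3 months on single questions; the text does not say. That stands, but such a comparison would be within a group and would not adjust the phase contrast.

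**Diagnosis is balanced by quota.** With 25 CHF and 25 COPD patients in each phase, diagnosis can confound only through differential attrition. This stands. Diagnosis is a secondary covariate, and the case rests on inclusion POS.

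**This is a feasibility study with a disclosed design limitation.** True, and it lowers the stakes. Disclosure does not, however, reduce a bias that data already collected could reduce.

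**A stronger reading does not hold.** A reader might infer that patients without 3-month data are dropped, because the listed tests cannot use a patient with no 3-month score and the attrition allowance suggests a completer analysis. The article says the reverse, that missing data will be included, and imputation before these tests is possible. The sentence lacks a method, which is detail an analysis plan may supply.

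**Conclusion.** The point holds as a weakness in the choice of analysis: no named between-phase comparison uses inclusion POS, although the phases are non-randomised and the score is collected in both. For r between 0.3 and 0.7, a 2-point imbalance at inclusion would shift the unadjusted 3-month difference by 0.6 to 1.4 points and raise the false-positive rate to about 7% to 16%. ANCOVA would lift power at 35 completers per group from 78.5% to about 82% to 97%.

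The sizes depend on the assumed correlation, the assumed imbalance, equal SDs of 6, and inclusion POS being completed before the intervention begins. That adjustment would help does not depend on the exact values.

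Two limits apply. Adjustment deals only with confounding carried by the measured covariates, so calendar-time changes and unmeasured differences remain. And a reader might infer that one mixed model could both adjust for inclusion POS as a covariate and retain patients who have inclusion data only. It cannot: with inclusion POS as a covariate such patients contribute no outcome, and with it as an outcome the unconstrained phase-by-time contrast has the change-score power of step 5. The 82% to 97% belongs to an ANCOVA in completers.

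**What to change.** State in the Data analysis section that the main between-phase analysis of 3-month POS total is an ANCOVA on phase, inclusion POS and diagnosis (CHF or COPD), reported as an adjusted mean difference with its 95% confidence interval. Keep the unadjusted test as a sensitivity analysis, and say that the adjusted estimate remains open to calendar-time and unmeasured confounding.

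The cost is a change of wording and a standard linear model, which SPSS can fit. No new data, patients or visits are needed. The price is an assumption of linearity in inclusion POS, which the unadjusted sensitivity analysis helps to put in context.
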